## Abstract

**Background:**

Hazardous and harmful consumption of alcohol is a leading cause of preventable disease and premature deaths. Modifying the amount and pattern of risky alcohol consumption conveys substantial benefits to individuals and to society at large. Telephone helplines provide a feasible alternative to face-to-face counselling in order to increase the reach of brief interventions aiming at modifying the hazardous and harmful use of alcohol. However, there is a lack of studies on the implementation and evaluation of population-based telephone services for the prevention and treatment of alcohol misuse.

**Methods/design:**

A randomised controlled trial was designed to compare a brief, structured intervention to usual care within the Swedish National Alcohol Helpline (SAH), concerning their effectiveness on decreasing the hazardous use of alcohol. Between May 2015 and December 2017, about 300 callers are to be individually randomised with a 1:1 ratio to a brief, structured intervention (*n* = 150) or to usual care (*n* = 150). The brief, structured intervention consists of the delivery of a self-help booklet followed by one proactive call from SAH counsellors to monitor and give feedback about the client’s progression. Callers assigned to usual care receive telephone counselling according to existing practice, i.e., motivational interviewing in a tailored and client-driven combination of proactive and reactive calls. The primary outcome is defined as a change from a higher to a lower AUDIT risk-level category between baseline and follow-up. General linear modeling will be used to calculate risk ratios of the outcome events. The primary analysis will follow an intention-to-treat (ITT) approach.

**Discussion:**

The trial is designed to evaluate the effectiveness in decreasing the hazardous and harmful consumption of alcohol of a brief, structured intervention compared to usual care when delivered at the SAH. The results of the study will be used locally to improve the effectiveness of the service provided at the SAH. Additionally, they will expand the evidence base about optimal counselling models in population-based telephone services for alcohol misuse prevention and treatment.

**Trial registration:**

ISRCNT.com, ID: ISRCTN13160878. Retrospectively registered on 18 January 2016.

**Electronic supplementary material:**

The online version of this article (doi:10.1186/s13063-017-2005-5) contains supplementary material, which is available to authorized users.

## Background

The consumption of hazardous and harmful amounts of alcohol is ranked as one of the leading preventable causes of premature death and disease. In 2015, the global disease burden attributable to alcohol was quantified to 85 million disability-adjusted life years (DALYs) and the cause of 2.3 million premature deaths. Since 1990, there has only been a small decreasing trend in alcohol use, revealing a major potential for interventions to reduce alcohol as a risk factor [1]. In 2015, 15% of the adult Swedish population were consumers of hazardous or harmful amounts of alcohol [2], corresponding to approximately 1.2 million individuals. In addition, the related societal costs of problem drinking are substantial, estimated at SEK20.3 billion (2002 prices) [3]. Consequently, these patterns of alcohol consumption constitute a key risk factor for morbidity in the Swedish population, calling for effective interventions.

Most individuals who consume hazardous amounts of alcohol or have alcohol dependence never seek health care [4], and a majority succeed in modifying their alcohol-related hazardous behaviour without professional support [5]. Although brief interventions (BI) in primary care settings are effective in reducing the consumption of hazardous and harmful amounts of alcohol [6, 7], their reach is limited since systematic recognition of problematic drinking is not pursued in most health care settings [8]. Because of their easy access, telephone services provide an ideal setting for the delivery of BI to consumers of hazardous amounts of alcohol.

Population-based quit lines are an established counselling setting in smoking cessation [9] and are readily available at low cost [10]. Although national or community alcohol helplines are established in several countries (e.g., New Zealand, the US, UK and Brazil), the evidence that the support provided by such a telephone service effectively modifies alcohol consumption remains scarce [11, 12]. In fact, to our knowledge, only one study has been published on population-based telephone counselling among persons with severe problems of alcohol abuse. The intervention was seemingly effective in promoting abstinence from alcohol. However, the study had methodological problems, especially an attrition close to 77% [11].

Apart from this example, telephone services for alcohol misuse have primarily been used within multicomponent interventions and/or interventions dedicated to clinical populations [13–17]. However, telephone services targeting consumers of hazardous amounts of alcohol in the general population could constitute an efficient complement to traditional health care, potentially reducing the barriers to treatment-seeking, for instance, by allowing protected identity of the user.

The Swedish National Alcohol Helpline (SAH) was established in 2007 in order to provide directly accessible toll-free counselling for users of hazardous and harmful amounts of alcohol. This setting offers the unique possibility of evaluating the effectiveness of telephone counselling open to the general population. An observational study of the SAH clients reported substantial improvements in the use of hazardous amounts of alcohol and in mental health at 12 months [12]. However, due to lack of a control group, no robust conclusions could be drawn on the effectiveness of the counselling.

Due to the pioneer stage of telephone-based services for alcohol misuse there is also a lack of knowledge on optimal duration, content, effectiveness and cost-effectiveness of the counselling provided. Studies suggest that the duration of BI may have marginal incremental effects on behavioural change [6]. Regarding the counselling method, there is evidence that face-to-face Motivational Interviewing (MI) efficiently decreases alcohol consumption [18], but whether the same effect could be achieved in telephone contacts is still a matter of speculation. Further, self-help materials appear as a promising tool for changing drinking behaviour [19]. In clinical and Internet-based BI such materials provided an effect that added to that of the principal counselling component [20, 21].

In order to contribute to the evidence base of telephone counselling for the consumption of hazardous amounts of alcohol, an individually randomised controlled trial (RCT) was designed at the SAH. The overarching aim of this study is to evaluate the effectiveness of a brief, structured intervention based on self-help followed by one proactive call compared to usual care in modifying drinking patterns. Usual care at the SAH consists of client-driven on-demand counselling with a varying number of proactive and reactive telephone calls based on MI. Secondary purposes of the trial are to compare the effects of the two types of counselling in other health domains such as mental health. In this paper we describe the study protocol of this RCT conducted at the SAH.

## Methods/design

The study is designed as a superiority, two-group RCT with follow-up at two time points (6 and 12 months). Clients are individually randomised with a 1:1 ratio to brief, structured intervention or usual care using a computer algorithm and allocation concealment. See Fig. 1 for a schematic overview of the trial. We follow the Standard Protocol Items: Recommendations for Interventional Trials (SPIRIT) Checklist for reporting the study protocol, attached as Additional file 1.

**Fig. 1 Fig1:**
[figure not shown]
Schematic overview from recruitment to follow-up endpoint of the randomised controlled trial (RCT) at the Swedish National Alcohol Helpline

### Setting

The trial is carried out at the SAH, a telephone service with national coverage that provides free-of-charge counselling on two to three parallel lines, operating 33 h per week, on weekdays. Written information about the SAH is readily available in health care settings, at the Internet and in social media. The SAH is financed by the Public Health Agency of Sweden and Stockholm County Council (SCC) that also holds the operational responsibility of the service.

In 2015, the SAH received 1849 calls from individuals who were consuming hazardous or harmful amounts of alcohol. There were 640 clients who called for the first time, 58% of whom were men. For first-time callers, the mean age was 48 years for men and 46 years for women (available for *n* = 415), and the mean Alcohol Use Disorder Identification Test (AUDIT) score was 21.1 and 21.5 for men and women, respectively (available for *n* = 407).

### Participants

#### Inclusion criteria

Clients are eligible to participate in the study if they:Are ≥18 years of age, the legal drinking age in SwedenAre first-time callers or callers with a ‘wash out’ period of at least 12 months since their last contact with the SAHAre seeking help for current use of hazardous or harmful amounts of alcohol (identified by a score of ≥6 for women and ≥8 for men on the AUDIT) [22]Are able to speak and read basic SwedishGive informed consent to be randomised into one of the counselling groups and to participate in the follow-up interviews

#### Exclusion criteria

Clients will be excluded from the study if they:At the time of the call exhibit the features of severe alcohol dependence in need of more intense treatment, as identified by SAH counsellors through a cumulative assessment combining a high score on the AUDIT, psychological comorbidities and a history of treatments for alcohol dependenceUse illicit drugsHave severe mental illness or suicidal intentionReport acute health problems in need of other treatment/medical care

Clients excluded from the study for any of the reasons above, or who wish to terminate participation, will receive counselling according to the SAH current treatment regimen or will be referred to other health care facilities. Concomitant care is permitted during the study period.

#### Trial arms

##### Brief, structured intervention

This intervention includes the delivery to participants of a self-help booklet followed by one proactive call from a counsellor at the SAH. The self-help booklet is designed as a guide to change alcohol use patterns using a cognitive behaviour therapy (CBT) framework. The booklet is developed by the Clinic for Alcohol and Health in Stockholm City, slightly modified for the SAH setting. The structure follows a step-by-step approach; starting from the clients’ initial reflections and motivation to change, proceeding to goal-setting and self-monitoring of their drinking behaviour. In addition, the material contains suggestions on how to practically accomplish behaviour avoidance and resistance skills. The booklet is provided by e-mail, mail or through a password-protected website. After 2 weeks from the dispatching of the booklet, the client is contacted by a proactive call from a counsellor at the SAH which has the scope to assess and guide the use of the material as well as to discuss the client’s progress. After the proactive call, no further contact with the client is initiated by counsellors at the SAH. However, clients are not discouraged from calling the SAH again if they feel the need to do so. If a further contact is initiated by the client, usual counselling is provided. The intervention is delivered according to a protocol and all contacts are logged in a computerised client record which is also used to monitor intervention adherence.

##### Usual care

Usual care provided at the SAH is based on MI, with components of CBT [23, 24]. The counselling aims to: develop resistance skills, promote the clients’ motivation to change and prevent recidivism into the use of hazardous amounts of alcohol. Sessions are tailored to the specific needs of each client such as the severity of their alcohol problems and their readiness to change. In practice, the number and duration of counselling sessions vary and the contact mode can be reactive (client-activated) and/or proactive (counsellor-activated). Clients may request contact with the same counsellor in subsequent calls. Since usual care admits multiple counselling sessions, each building on the outcome of the previous one, all client contacts are registered in a computerised client record. Adherence to the agreed contacts is monitored using information from client records. Since usual care is client-activated, there is no standardised protocol for the counselling.

##### Qualification of counsellors

Counsellors at the SAH are qualified within health care or health promotion and receive training in MI as well as education about the consequences and effects of alcohol use prior to employment. The training consists of a 14-day programme of which six are full days of MI training, distributed over a 4-month period. The MI teaching includes 2.5 days of practical training using recorded interviews with simulated clients and group feedback sessions. The counsellors’ MI performance is evaluated throughout training and employment by coding according to the Motivational Interviewing Treatment Integrity (MITI) Code Version 3.1 [25] conducted at the Motivational Interviewing Coding Laboratory (MIC Lab) at the Karolinska Institutet in Stockholm.

### Outcomes

#### Primary outcome

The primary outcome will be measured at the 6- and 12-month follow-up, through the alcohol screening instrument, AUDIT, validated to identify problematic alcohol use at the lower end of the spectrum, i.e., hazardous and harmful use [26, 27]. AUDIT encompasses three domains: the use of hazardous amounts of alcohol, dependence symptoms and harmful alcohol use. It consists of 10 questions each scored from 0 to 4, thus yielding a maximum scale score of 40. The scale score can be divided into risk levels: ‘Low risk’ (score 0–7 for men and 0–5 for women), ‘Hazardous alcohol use’ (8–15 for men and 6–13 for women), ‘Harmful alcohol use’(16–19 for men and 14–17 for women) and ‘Highly problematic alcohol use’ (≥20 for men and ≥ 18 women) [22].

The primary outcome in this study is defined as a downward shift in AUDIT risk level (yes/no) between baseline and follow-up. The proportion of participants undergoing this shift will be used to aggregate the data.

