### Sample size

The sample size estimation is based on the primary outcome, i.e., decrease in AUDIT risk category, in a superiority design. Based on a previous observational study of the SAH [12], we estimate that 30% in the usual care group will make a downward shift in AUDIT risk level. We estimate that 300 participants will be recruited to the study, of which at least 250 participants will be included in the analytical sample (125 in each experimental group). Based on the analytical sample the study will have more than 90% statistical power to detect a Risk Ratio (RR) equal to or greater than 1.7 for the alternative counselling (i.e., 50% cumulative rate of change in the brief, structured intervention group) as statistically significant at the 5% level. For a RR of 1.3 the power will decrease to about 50%.

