#### Statistical analysis

The primary outcome ‘change in AUDIT risk level’ will be analysed as a dichotomous variable where any downward shift (yes/no) from a higher- to a lower-risk level between baseline and follow-up is considered as a clinically meaningful change in drinking habits. The ratio of the cumulative rates of change in the trial groups will constitute the effect measure of the brief, structured intervention versus usual care. General linear models (GLM) will be used to calculate the RR for the outcome event.

Baseline characteristics will be compared between groups in order to detect potential imbalance in predictors of the outcome. If the two groups are not well balanced according to these predictors, multivariable analysis applying logistic regression models will be carried out to estimate odds ratios for the outcome event.

Secondary outcomes (i.e., depression, anxiety, health measures, care seeking) will be analysed using GLM or logistic regression models as described above.

Complementary ‘per-protocol’ and ‘as-treated’ analyses will also be conducted [30]. The ‘per-protocol’ analysis, will only include participants with complete adherence. Complete adherence is defined as: having used the material and received the proactive call (brief, structured intervention); receiving all counselling sessions agreed between the counsellor and the client (usual care). In the ‘as-treated’ analysis, the number of sessions and total duration of the counselling will be considered for each participant, independent of group allocation. These analyses will contribute to the assessment of the effect of the intervention when delivered in standard practice. Possible confounding effects must be carefully monitored in these analyses, since they ignore the random assignment and, therefore, the distribution of baseline risks between participants.

Moderating factors in the analysis include readiness to change, as well as dose-response, i.e., number and length of calls. Further, process data from the records will provide information on the conduct of the proactive calls (adherence).

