### Dissemination of results

Outcome results will be disseminated in peer-reviewed journals with minimal time from the completion of data collection. Results will be reported separately for the 6-month and the 12-month follow-up. Results will be made available to the contributors and participants of the study, as well as to the funding agency and to the administrators of the SAH through the appropriate websites. No interim analyses are planned.

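### The primary outcome has two follow-up visits, 6 and 12 months, and the protocol names no primary visit, testing order or split of the 5% level

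*Protocol article*

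**What the plan says.** All references are to the protocol article.

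- **Primary outcome:** "The primary outcome will be measured at the 6- and 12-month follow-up, through the alcohol screening instrument, AUDIT". The outcome is "defined as a downward shift in AUDIT risk level (yes/no) between baseline and follow-up", with no visit named.
- **Statistical analysis:** the event is "any downward shift (yes/no) from a higher- to a lower-risk level between baseline and follow-up", and "The ratio of the cumulative rates of change in the trial groups will constitute the effect measure". No visit is named, and no model combines the two visits.
- **Dissemination of results:** "Results will be reported separately for the 6-month and the 12-month follow-up".
- **Sample size:** "we estimate that 30% in the usual care group will make a downward shift in AUDIT risk level". This is set against 50% in the brief intervention arm, with 125 analysed per arm and more than 90% power to detect the difference "as statistically significant at the 5% level". The section does not say to which visit the 30% and 50% apply.

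Two places lean towards 12 months without making it primary. The Discussion describes the aim as long-term effectiveness, and the missing-data section applies last observation carried forward to the long-term follow-up.

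**The concern.** The time point is part of the definition of a primary outcome. Here two visits share primary status, each gets its own reported result, and only one 5% comparison was planned for. That leaves two routes to a superiority claim. It also leaves no rule for the case where the arms differ at one visit and not at the other.

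The stake is practical. The Discussion says that superiority of the brief intervention would be a strong reason to move the helpline to the less labour-intensive method. A reader of the results should be able to tell in advance which comparison that decision rests on.

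**Working it through.** **Inputs.** From Sample size: 30% versus 50%, 125 analysed per arm, 5% level. Assumed: two-sided testing (sidedness is not stated) and the correlation between the 6- and 12-month test statistics (not given). The same participants and the same baseline enter both tests, so the correlation should be positive; 0.3 to 0.8 is used as the working range.

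**1. The plan's own power figure (pooled-variance normal approximation).**
- Pooled proportion: (0.30 + 0.50)/2 = 0.40.
- SE under the null: √(2 × 0.40 × 0.60/125) = 0.06197.
- SE under the alternative: √((0.30 × 0.70 + 0.50 × 0.50)/125) = 0.06066.
- Power: Φ((0.20 − 1.960 × 0.06197)/0.06066) = Φ(1.295) = 90.2%.

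The stated figure therefore reproduces as one test, at one visit, at 5%.

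**2. Error if both visits were tested at 5% and either could carry the claim.** With (Z1, Z2) bivariate normal with correlation ρ under the null:
- two-sided family-wise error = 1 − P(|Z1| < 1.96, |Z2| < 1.96);
- chance of at least one false result favouring the brief intervention = 1 − P(Z1 < 1.96, Z2 < 1.96).

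| ρ (assumed) | Two-sided family-wise error | False result favouring the brief intervention |
|---|---|---|
| 0 | 9.75% | 4.9% |
| 0.3 | 9.5% | 4.8% |
| 0.5 | 9.1% | 4.5% |
| 0.6 | 8.8% | 4.4% |
| 0.8 | 7.8% | 3.9% |
| 1 | 5.0% | 2.5% |

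The ρ = 0 row follows directly: 1 − 0.95² = 9.75% and 1 − 0.975² = 4.9%. The reference for a single two-sided 5% test is the last row.

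**3. What each remedy does to power.**
- One primary visit, or a fixed testing order: the (first) test keeps 5%, so power stays at 90.2%.
- Bonferroni, 2.5% two-sided at each visit: Φ((0.20 − 2.241 × 0.06197)/0.06066) = Φ(1.007) = 84.3%. Holding 90% would take 147 analysed per arm (294 in total) against the planned 125 (250).

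**The case against.** The strongest reply is that the article never says each visit is tested at 5%, nor that significance at either visit would establish superiority. The 5% appears only in Sample size, separate reporting is not separate confirmatory testing, and multiplicity rules are often left to an analysis plan, which is not shown here. This stands in part: the error rates above are conditional on an inference and are labelled so. It does not remove the gap. Which visit defines the primary outcome belongs to the outcome definition, and the article sets two visits rather than staying silent.

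It is also fair that the hypothesis is directional (Statistical methods: the brief intervention is more effective). The two-sided range counts false results favouring usual care as well. The error relevant to a wrong superiority claim is about half as large, and both columns are therefore given.

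Two stronger readings are tempting, and the article does not support them.

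- A reader might take the *cumulative rates* wording to mean a shift at either visit, so that someone who improved at 6 months and relapsed by 12 counts as a success. However, Primary outcome aggregates the data as the proportion who shift, and Sample size uses the 50% cumulative rate as the counterpart of the 30% who shift. It reads most naturally as a loose synonym.
- A reader might infer from separate reporting that 6-month results will be analysed and published while 12-month interviews continue. The article says twice that no interim analyses are planned, and it ties dissemination to completion of data collection. Early release is possible on the wording but is not a stated plan.

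**Conclusion.** The point holds in this form: the primary outcome has two visits, and no primary visit, testing order or alpha split is named. The primary result is therefore not uniquely defined, and a split result has no agreed conclusion. That part rests on the text alone.

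The size is conditional. If each visit were tested at two-sided 5% and either could support superiority, the family-wise error would be about 7.8% to 9.5%, and the false-positive chance favouring the brief intervention about 3.9% to 4.8% instead of 2.5%, for assumed correlations of 0.8 down to 0.3. It would be wrong to say that the article prescribes two tests at 5% each, or that its type I error is known to exceed 5%. What it does is leave that route open.

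**What to change.** Before any between-arm outcome comparison, do one of the following.

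1. **Name one visit as the single primary time point and make the other secondary.** Twelve months is a reasonable choice. It fits the long-term aim in the Discussion, and the observational study cited for the 30% rate is described in the Background as reporting at 12 months. The choice is not dictated, because Sample size does not tie the 30% to a visit.
2. **Test the two visits in a fixed, stated order**, the second only if the first is significant.

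Either keeps the 5% level and about 90% power at the first test, so the Bonferroni loss to 84.3% need not be incurred. In both cases, state in Sample size which visit the 30% and 50% refer to, and in Sample size and Statistical analysis replace the cumulative-rate wording with the proportion shifted at that visit.

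**Cost:** a short amendment and no new data. The other visit loses confirmatory status under option 1, or is confirmatory only if the first test succeeds under option 2. Trial status describes recruitment as ongoing; the choice is credible only if made before arm-level outcomes are seen.
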